**Methods:**

Phase 1 will evaluate the most effective cleaning procedure, while phase 2 will correlate oral hygiene to VAP incidence. At the start of phase 1, the ICU patients will be randomly allocated into three different groups (10 patients/group): the efficacy of chlorhexidine, classical MB-PDT, and mouthwash MB-PDT will all be measured for the quantification of viable bacteria, both pre- and post-treatment, by a Reverse Transcription Polymerase Chain Reaction (RT-PCR). In phase 2, the most effective procedure found in phase 1 and a mechanical cleaning with filtered water will be carried out daily, once a day, over 5 days, with a total of 52 ICU patients randomly allocated into the two groups. The clinical records will be evaluated in order to find any pneumonic diagnoses.

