### Sample size calculation

First, a published paper using the same method of sample analyses (PCR + PMA pre-treatment) is to be used to determine the effect size (*Δ*). The largest and the smallest mean values (1.69 and 0.27, respectively), as well as the standard deviation (*σ* = 0.36) of the PCR quantification of living bacteria using PMA were taken from the Àlvarez article, 2013 [50]. The *n* value is to be the number of treatment groups, i.e., 3:$$ \varDelta =\frac{Largest- smallest}{{\left(\frac{\sigma }{\sqrt{n}}\right)}^2}=\frac{1.69-0.27}{{\left(\frac{0.36}{\sqrt{3}}\right)}^2}=32.8 $$

G*Power software (version 3.1.9.2, Dusseldorf, Germany) was used to calculate the sample size. Using the calculated effect size, *F* tests will be chosen for the repeated measures and for the within-between interactions. Three groups will be studied and each group will be measured before and after the oral-hygiene procedures (i.e. three groups and two measurements). The sample size was determined by setting a two-sided error at 5% and the test power at 95% of the test. According to the calculations, a sample of six patients per group will be necessary in order to detect the differences in oral hygiene in phase 1. When considering this result and the possibility of difficulties in the sample processing, phase 1 will be conducted with 10 patients per group.

The sample size calculation for phase 2 was based on the percentages of patients with VAP before and after the implementation of oral-dental care, as published by Garcia et al. [8]. Using G*Power software, when choosing the Exact Family Test and Fisher’s Exact Test as statistical tests (inequality, two independent groups) and by inserting the proportions of 0.086 and 0.041 [8], the sample size was found to be 52, i.e. 26 patients per group. It is important to highlight that at this phase, a 5-day protocol will be evaluated. Due to the condition of the patients, some of them may recover and the mechanical ventilation will be removed, while some may get worst or even die. Due to these potential dropout patients, a sample size of 70 patients (35 per group) will be used.

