### Sample size

In phase 1, 30 patients will be divided into three experimental groups (10 patients per group: chlorhexidine, classical MB-PDT and mouthwash MB-PDT). In phase 2, a total of 70 patients will be selected, 35 patients in each experimental group.

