### Data analysis plan

The studied parameters in this work will aim to follow a Gaussian (normal) distribution and they will be verified by the Shapiro-Wilk test. Where the data are not parametric, they will be transformed by using a logarithm or any other math transformation into normally distributed data. In this manner, parametric methods will be used in order to detect the differences among the groups. In order to show the actual distribution of the measured data, a graph based on the mean values and standard deviations will be used. For the data analyses, SPSS Statistics^TM^ Version 22 Software (IBM, Armonk, NY, USA) will be used. The statistical analyses will be realised by using analysis of variance (ANOVA): this will include the repeated measures as well as the within- and between-group interactions since three groups will be studied and each group will be measured before and after the oral-hygiene procedures. The frequencies of VAP occurrence will be measured in the two groups: (1) the most effective procedures found in phase 1 group and (2) the mechanical cleaning with filtered water group. The chi-square test will be used to verify the difference between the observed frequencies. The significance level for all of the tests will be *p* < 0.05. The results of this study will be published in an international journal.

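### The phase 2 sample size of 52 does not follow from VAP rates of 0.086 and 0.041; those rates need about 492 per group for 80% power, not 26

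*Protocol article*

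**What the plan says.** The section Sample size calculation takes its phase 2 inputs from a published before-and-after study; they are "based on the percentages of patients with VAP before and after the implementation of oral-dental care". It names the software (G*Power) and the test: "when choosing the Exact Family Test and Fisher’s Exact Test as statistical tests (inequality, two independent groups". The result is given as "by inserting the proportions of 0.086 and 0.041 [8], the sample size was found to be 52, i.e. 26 patients per group". The total is then raised to 70 (35 per group) because some patients are expected to be extubated, to deteriorate or to die during the 5 days.

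No power or sidedness is given for phase 2. The only such statement, "setting a two-sided error at 5% and the test power at 95% of the test", stands in the phase 1 paragraph. The Data analysis plan compares VAP frequencies with a chi-square test, without saying whether it is continuity-corrected, and sets the significance level at 0.05 for all tests. The VAP rate is the main phase 2 outcome (Outcomes).

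The total appears in two forms. The abstract describes phase 2 "with a total of 52 ICU patients randomly allocated into the two groups". The section Sample size says: "In phase 2, a total of 70 patients will be selected, 35 patients in each experimental group".

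**The concern.** Rates of 8.6% and 4.1% differ by 4.5 percentage points, and both are low. With 26 patients per group one expects about two cases against one, and no standard test can separate those reliably. A total of 52 is therefore implausible on sight.

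Phase 2 is the part of the trial that links oral hygiene to VAP, and the article presents it as sized for that outcome. If the size does not follow from the stated effect, readers, the ethics committee and the registry are given an assurance of power that the trial lacks. A null result could then be taken as evidence that the procedure does not work.

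**Working it through.** **Inputs.** p1 = 0.086, p2 = 0.041, Fisher's exact test, equal groups, 26 per group before and 35 after the dropout allowance (Sample size calculation); chi-square at 0.05 (Data analysis plan). Phase 2 power and sidedness are not stated, so several values were tried.

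**1. Trying to reproduce 52.** Fisher power is the sum, over all pairs of case counts (a, b), of Bin(a; n, p1) × Bin(b; n, p2), counting only pairs with p ≤ 0.05. The smallest n per group that reaches each power, with the total in brackets:

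| Power | Two-sided 5% | One-sided 5% |
|---|---|---|
| 80% | 492 (984) | 397 (794) |
| 90% | 642 (1284) | 532 (1064) |
| 95% | 784 (1568) | 658 (1316) |

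The stated 52 is too small by a factor of 984/52 = 18.9 (80% power) to 1568/52 = 30.2 (95%), two-sided.

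The normal approximation is a cross-check: n = [z(α/2)·√(2p̄(1−p̄)) + z(β)·√(p1(1−p1) + p2(1−p2))]² / (p1−p2)². With p̄ = 0.0635 and 80% power, this is (1.960 × 0.3449 + 0.842 × 0.3434)² / 0.045² ≈ 0.931/0.002025 ≈ 460 per group, or 920 in total (1008 with continuity correction). The most lenient variant tried (one-sided 10%, 50% power, no correction) still needs 194.

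**2. What does give 52.** With 0.86 and 0.41, Fisher's test gives 26 per group in two settings:
- two-sided 5%, 90% power: 0.895 at 25 per group, 0.911 at 26;
- one-sided 5%, 95% power: 0.944 at 25 per group, 0.954 at 26.

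Two-sided 5% with 95% power would give 31 per group (62). Shifting the decimal in only one proportion does not give 52: with two-sided Fisher at 80% power or more, 0.86 against 0.041 needs 14 to 16 in total and 0.086 against 0.41 needs at least 62.

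**3. Power at the stated rates, two-sided 5%, exact enumeration:**

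| Test | 26 per arm | 35 per arm |
|---|---|---|
| Fisher (used for sizing) | 0.9% | 2.1% |
| Chi-square, uncorrected | 7.1% | 11.3% |
| Chi-square, Yates | 0.7% | 2.1% |

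One-sided Fisher gives 3.1% and 5.3%. The highest two-sided figure leaves 100 − 11.3 = 88.7% probability of a non-significant result.

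**4. Information available.** Expected cases are 26 × 0.086 = 2.2 against 26 × 0.041 = 1.1, or 3.0 against 1.4 with 35 per arm. Two-sided Fisher needs at least 6 against 0 at either size. The 95% half-width for the risk difference, 1.96·√[(0.086 × 0.914 + 0.041 × 0.959)/n], is 13.2 points with 26 per arm and 11.4 with 35, against a planned difference of 4.5.

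**5. What these sizes can detect** (two-sided Fisher, 80% power): about 4% against 31%, or 9% against 39%, with 35 per arm; about 4% against 36% with 26 per arm.

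**The case against.** The arithmetic of the core point is not open to dispute, but several stronger readings are tempting and should be resisted.

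- **That the planned analysis has 1 to 2% power.** This holds for Fisher, which the article names only for sizing. The planned test is chi-square; uncorrected, it has about 7 to 11%. Only with Yates correction does it fall to 0.7 and 2.1%, and the article does not say which version applies. Any power statement must name its test.
- **That a one-sided calculation was run despite the word inequality.** A one-sided setting reproduces 52 only if the 95% power is borrowed from the phase 1 paragraph. A two-sided test at 90% power reproduces it equally exactly. The documents do not settle which was used.
- **That the decimal slip is established.** No software output is shown. The match is close and the slip is easy to make with percentages, but it remains an inference. The failure to reproduce 52 does not depend on it.
- **That a null result is certain.** This is conditional on 8.6% and 4.1%. The Discussion cites 25% and about 19% from a systematic review, and pneumonia is recorded on any one of several criteria, so observed rates may differ.
- **That 52 against 70 is a second sizing error.** The methods explain it: 52 is before dropout and 70 after. Only the abstract's statement that 52 are randomised is wrong, and that is editorial.

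It could also be said that the missing power and sidedness belong in a fuller document. That would matter if some reasonable choice gave 52, and none does.

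**Conclusion.** The stated phase 2 sample size is wrong for its stated inputs and should be corrected before recruitment. At two-sided 5%, about 492 per group are needed for 80% power and about 784 for 95%, against 26 stated. The increase to 35 covers expected losses and does not repair power; 26 is the planned analysable number. If the stated rates hold, the chance of significance is about 11% at best with the planned test and about 2% or less with Fisher, so a non-significant result would say almost nothing about whether the procedure works.

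The result rests on the two rates as the article prints them (the source study was not available), equal groups, independent patients, and no losses in the figures for 35 per arm.

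**What to change.** In Sample size calculation:
- Delete the statement that 52 (26 per group) follows from 0.086 and 0.041.
- State the power at those rates for both 26 and 35 per arm, naming the test: about 1 to 2% for two-sided Fisher, about 7 to 11% for uncorrected chi-square.
- Describe phase 2 as exploratory, reported as a risk difference with a 95% confidence interval, and state that a non-significant p-value will not be read as no effect.
- If a detectable difference is given, use the two-sided Fisher figures at 80% power: about 4% against 31% or 9% against 39% with 35 per arm, and about 4% against 36% with 26 per arm.

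In the abstract, give 70 as the number randomised; 52 is the figure before dropout.

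The cost is wording in two places and an entry in the registry update that Trial status already announces; no extra patients are needed. If the sponsor wants a confirmatory comparison at these rates instead, phase 2 would have to be re-sized to roughly 984 patients for 80% power by two-sided Fisher, before dropout. Trial status says that recruitment has not begun, so either course is still open.

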### Sample size

In phase 1, 30 patients will be divided into three experimental groups (10 patients per group: chlorhexidine, classical MB-PDT and mouthwash MB-PDT). In phase 2, a total of 70 patients will be selected, 35 patients in each experimental group.

### Inclusion/exclusion criteria

The inclusion criteria are: ICU patients with 0- to 24-h orotracheal intubation; patients whose family signs the Consent Form; both genders, aged above 18 years old; and edentulous. The exclusion criteria are: reintubation; readmission in the ICU; smokers and ex-smokers for less than 5 years.

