## Background

It has been proposed that the oral cavity may be the dissemination focus of potentially pathogenic organisms to other body locations [1–4]. In intensive care units (ICU), infectious diseases are prevalent and they are responsible for the high mortality index of inpatients. The lung is the most affected organ mainly due to mechanical ventilation [5]. Ventilator-associated pneumonia (VAP) is defined as pneumonia in a patient receiving mechanical ventilation for at least 48 h that is not pre-existent at the moment of intubation [6]. The most prevalent pathogenic agents related to pneumonia are *Pseudomonas aeruginosa* 30.1%), *Staphylococcus aureus* (19.6%), *Acinetobacter* spp. (13.0%), *Klebsiella* spp. (9.5%) and *Enterobacter* spp. (8.4%) [7]. Both VAP control and prevention are important in an ICU since this can reduce hospitalisation time and costs [8].

During a patient’s stay in an ICU, oral biofilms and tongue coating increase simultaneously. Due to the orotracheal intubation, a patient’s mouth is open during the entire period, increasing bacterial plaque formation and reducing saliva flow. Consequently, this reduces the innate defence system and increases the risk of VAP [5]. Therefore, oral hygiene in an ICU is essential when implementing VAP-prevention strategies. However, developing these new strategies is a challenge, since many substances that have been suggested are associated with bacterial resistance; for example, chlorhexidine [9, 10].

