**Fig. 1 Fig1:**
[figure not shown]
Phase-1 flow diagram

#### Interventions in phase 2

Based upon the results generated in phase 1, a new group of patients will comprise phase 2 of this study. Here, the oral-hygiene procedures described above will be performed in two groups of patients: (1) the most effective procedures in phase 1 group and (2) the mechanical cleaning with filtered water group. These procedures will be performed daily, over 5 days, when the outcomes will be evaluated. The clinical records will be checked and the pneumonia diagnoses will be determined by at least one of the following criteria: oximetry; body temperatures above 38 °C or below 35 °C; a leukocytosis or a leukopenia (leukocytes) count in the peripheral blood that is below 4000/mm^3^ or above 11,000/mm^3^; the existence of new, persistent or progressive lung infiltrates, or pleural effusion [51–54]. If any of the patients present an adverse reaction, they will be removed from the study and this will be reported in the published results paper. All of the personal information of the patients will be kept confidential. Figure 2 will describe the complete flow diagram for phase 2.

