### Outcomes

Phase 1: the main outcome will be the efficacy of the oral-hygiene procedures, evaluated by the total bacteria count, before and after the treatments (three groups and two time points). A secondary outcome that can be measured is the change in the pathogenic bacteria count that is related to VAP after the oral-hygiene procedures.

Phase 2: the main outcome will be the rate of VAP, evaluated by checking the medical cards, 5 days after the daily oral-hygiene procedures.

The detailed schedule for the study is presented in the SPIRIT figure (Fig. 3).

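### Phase 2 enrols within 24 h of intubation with no requirement on expected ventilation, although VAP is defined as needing at least 48 h, so some randomised patients cannot be cases under that definition

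*Protocol article*

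**What the plan says.** All places are in the protocol article.

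- **Inclusion/exclusion criteria.** One list serves both phases. The only ventilation-related inclusion criterion is "ICU patients with 0- to 24-h orotracheal intubation". The exclusions do not mention duration: "The exclusion criteria are: reintubation; readmission in the ICU; smokers and ex-smokers for less than 5 years".
- **Background.** VAP is defined as "pneumonia in a patient receiving mechanical ventilation for at least 48 h", and it must not have been present at intubation.
- **Outcomes.** For phase 2, "the main outcome will be the rate of VAP, evaluated by checking the medical cards, 5 days after the daily oral-hygiene procedures".
- **Interventions in phase 2.** The procedure is given daily for 5 days. For the outcome, "the pneumonia diagnoses will be determined by at least one of the following criteria"; the signs listed are oximetry, temperature, leukocyte count, and lung infiltrates or pleural effusion. No minimum ventilation time is attached.
- **Sample size calculation.** The phase 2 number was obtained "by inserting the proportions of 0.086 and 0.041", giving 26 per group. The section then foresees that "some of them may recover and the mechanical ventilation will be removed". It groups these patients with those who worsen or die as potential dropouts, and raises the total from 52 to 70. It does not say whether they are replaced, excluded, or counted as free of VAP.

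**The concern.** The entry criteria fit phase 1 but not the phase 2 endpoint. A patient enters phase 2 between 0 and 24 h after intubation, so must stay ventilated for a further 24 to 48 h before a pneumonia can be VAP in the Background sense. Nothing at entry selects for that. Someone expected to be extubated the next day is eligible, is randomised, receives only one or two of the five daily procedures, and cannot become a case by that definition in either arm.

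The protocol foresees early extubation but answers it only by randomising more patients. Whichever way those patients are later handled, the VAP comparison suffers: through a smaller absolute difference, through events that are not VAP by the protocol's definition, or through losing patients after randomisation.

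**Working it through.** **Inputs.** Planned VAP proportions 0.086 and 0.041; 26 per group before and 35 per group after the dropout allowance (all from Sample size calculation); 5% significance level (Data analysis plan). Two inputs are assumptions: the share q of randomised patients extubated before 48 h, which the protocol does not give, taken as 10% to 40%; and that 0.086 and 0.041 describe patients ventilated long enough to be at risk.

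**Step 1: the plan's own figure.** For two proportions, two-sided 5%, the n per group is

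[1.960·√(2·p̄·(1−p̄)) + z_power·√(p1(1−p1) + p2(1−p2))]² / (p1−p2)², with p̄ = 0.0635.

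No power is stated for phase 2. At 80% power (z = 0.842) this gives (0.676 + 0.289)² / 0.045² ≈ 460 per group; at 95% it gives 761. The stated 26 per group does not reproduce: 460/26 ≈ 17.7. That is a separate and much larger problem, and it sets the scale for this one. The allowance is (70 − 52)/70 = 25.7%, covering recovery, worsening and death together.

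**Step 2: early-extubated patients kept as non-cases.** Their risk is zero in both arms, so each proportion is multiplied by (1−q):

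| q | At risk per arm, 35(1−q) | Rates | Difference, 4.5(1−q) points | n per group, 80% power |
|---|---|---|---|---|
| 0 | 35 | 8.6% / 4.1% | 4.50 | 460 |
| 10% | 31.5 | 7.7% / 3.7% | 4.05 | 515 |
| 20% | 28 | 6.9% / 3.3% | 3.60 | 583 |
| 30% | 24.5 | 6.0% / 2.9% | 3.15 | 671 |
| 40% | 21 | 5.2% / 2.5% | 2.70 | 788 |

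The risk ratio stays at 4.1/8.6 = 0.48. At 35 per group, approximate power goes from 11.6% (q = 0) to 8.5% (q = 40%); exact Fisher power goes from 2.1% to 0.4%.

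**Step 3: counted under the phase 2 diagnosis rule.** That rule has no 48 h condition, so a short-ventilated patient with one listed sign can be recorded as a case. If the chance r of this is the same in both arms, the rates become p(1−q) + r·q. The difference is again 4.5(1−q) points, but the rates no longer need fall, and part of the events are not VAP under the Background definition.

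**Step 4: dropped.** The planned rates are not diluted, but the arms shrink from 35 to 35(1−q); at the full 25.7% allowance that is 26 per arm. The groups compared are then selected on something that happened after randomisation.

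**The case against.** The strongest reply is that the harm depends on choices the protocol leaves open. The 48 h condition stands only in the Background, while the rule used to count phase 2 outcomes lacks it. A reader might infer that early-extubated patients can never be recorded as VAP; as the rule is written, they can. A reader might also infer that the comparison is necessarily diluted. That follows only if these patients stay in the denominator as non-cases, whereas Sample size calculation calls them potential dropouts. Both points stand, which is why the three routes are set out separately above.

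The size is also not documented. The share extubated before 48 h is not given. The 25.7% allowance is no estimate of it, because it covers other causes and all 5 days. The planning rates are described only as percentages with VAP before and after oral-dental care; if their denominator already included short-ventilated patients, the dilution is already in them. Nor do zero-risk patients add noise in the binomial sense: the variance falls, from 0.086 × 0.914 = 0.079 to 0.052 × 0.948 = 0.049 at q = 40%. What is lost is absolute difference and events.

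Finally, early enrolment without a forecast is a legitimate inclusive design, and the phase 2 flow diagram, which might carry phase-specific entry detail, is not available here.

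These points limit the size and certainty of the harm. They do not remove the mismatch, because each way of handling these patients worsens the comparison and selecting at entry lessens every one.

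**Conclusion.** The point holds as a mismatch between the phase 2 entry criteria and the protocol's definition of its endpoint. Patients extubated before 48 h can be randomised and cannot be VAP cases under the Background definition. The consequence is a smaller difference, misclassified events, or exclusions after randomisation, depending on handling that the protocol does not fix.

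The range of 4.05 to 2.70 points is illustrative. It rests on the assumed q and on the at-risk reading of the planning rates. It would be wrong to conclude that this omission explains the weakness of phase 2, or that a new criterion would cure it: with no early extubation at all, approximate power at 35 per group is only 11.6%. The point keeps its value once the sample size is corrected. At q = 20%, retaining these patients as non-cases would cost 583 − 460 = 123 more patients per group at 80% power. It is a worthwhile, inexpensive correction of secondary importance.

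**What to change.** 1. Add a phase 2-only inclusion criterion: the treating team expects mechanical ventilation to continue for at least 48 h from intubation. Record it before the envelope is opened, so that it uses only information available before allocation and cannot differ by arm. Leave phase 1 eligibility unchanged.
2. State that all randomised phase 2 patients stay in the main analysis, including those extubated sooner than forecast, and remove the implication that they are dropouts.
3. Reconcile the diagnosis rule in Interventions in phase 2 with the 48 h definition in Background, so that one case definition governs the endpoint.

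The cost is one eligibility line, one tick-box and two clarifying sentences, with no added patients, staff or procedures. The downsides are an imperfect forecast and somewhat slower recruitment, in a single ICU already limited to edentulous patients and excluding smokers and recent ex-smokers. Trial status says that recruitment has not started, so the change can still be made before any patient is enrolled.

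### Phase 2 entry criteria do not exclude pneumonia present at intubation, although the protocol defines VAP as not pre-existent: such patients can be randomised, counted as cases under the current outcome rule, and dilute the absolute difference if that rule is repaired

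*Protocol article*

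**What the plan says.** All references are to the Protocol article.

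- **Inclusion/exclusion criteria** gives one list, not split by phase: "The inclusion criteria are: ICU patients with 0- to 24-h orotracheal intubation; patients whose family signs the Consent Form", with age above 18 and edentulism as the other conditions. It continues: "The exclusion criteria are: reintubation; readmission in the ICU; smokers and ex-smokers for less than 5 years". Neither part mentions pneumonia or respiratory infection at entry.
- **Background** defines VAP as pneumonia in a patient who has had "mechanical ventilation for at least 48 h that is not pre-existent at the moment of intubation".
- **Interventions in phase 2** says that "a new group of patients will comprise phase 2 of this study" and adds no entry criterion. It then says that "the pneumonia diagnoses will be determined by at least one of the following criteria". The list covers oximetry, temperature, leukocyte count and "the existence of new, persistent or progressive lung infiltrates, or pleural effusion". No item is compared with the patient's state at entry.
- **Outcomes**, for phase 2: "the main outcome will be the rate of VAP, evaluated by checking the medical cards, 5 days after the daily oral-hygiene procedures".
- **Sample size calculation** uses proportions of 0.086 and 0.041, states 26 patients per group, and raises this to 35. The reasons given for the increase are extubation after recovery, deterioration and death. Pneumonia at entry is not among them.

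**The concern.** The definition in the Background restricts the outcome to pneumonia that begins after intubation. The entry criteria do not restrict the population to match. A patient intubated with pneumonia meets every stated criterion and may be randomised in phase 2.

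Two things can follow. Under the outcome rule as written, such a patient can be a case from the first day in either arm, because one sign is enough and a persistent infiltrate qualifies. If the outcome rule is tightened to require new disease, the patient is no longer a case but remains in the denominator with little or no chance of a new event. Repairing the outcome rule therefore does not remove the entry problem. At stake are the absolute difference, the power to detect it, and the balance of such patients between two arms of 35.

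**Working it through.** **Inputs.** Planned rates p1 = 0.086 and p2 = 0.041, and 35 per arm, come from Sample size calculation. The share s of entrants with pneumonia at intubation is not in the article; 10%, 20% and 30% are assumed. It is also assumed that the two rates refer to patients free of pneumonia at entry.

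**The plan's own figures.** The planned difference is 0.086 − 0.041 = 0.045 (4.5 points), and the risk ratio is 0.041/0.086 = 0.48. The usual normal-approximation formula for two proportions, where p̄ is the mean of the two rates, is

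n per arm = [z₀.₉₇₅√(2p̄(1−p̄)) + z₀.₈₀√(p1(1−p1) + p2(1−p2))]² / (p1−p2)²

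With the planned rates this is (1.960 × 0.3449 + 0.8416 × 0.3434)² / 0.045² = 0.9311/0.002025, so 460 per arm. The stated 26 per arm is not reproduced at 80%, 90% or 95% power, one- or two-sided, with or without continuity correction; the smallest result is 363 per arm. The sample-size error is a separate matter. The 460 serves here only as a baseline for the dilution.

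**Case A: outcome rule repaired, entry criteria unchanged.** If patients with pneumonia at entry supply no new events, each rate becomes (1−s)p.

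| s | Rates | Difference | Risk ratio | n per arm (80% power, two-sided 0.05) |
|---|---|---|---|---|
| 0 | 8.6% vs 4.1% | 4.5 points | 0.48 | 460 |
| 10% | 7.74% vs 3.69% | 4.05 points | 0.48 | 515 (+12%) |
| 20% | 6.88% vs 3.28% | 3.6 points | 0.48 | 583 (+27%) |
| 30% | 6.02% vs 2.87% | 3.15 points | 0.48 | 671 (+46%) |

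The factor (1−s) cancels in the ratio, so the risk ratio does not move. If some of these patients do have a distinct later VAP, the loss is smaller than shown.

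**Case B: outcome rule as written, all such patients counted.** Each rate becomes s + (1−s)p.

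| s | Rates | Difference | Risk ratio |
|---|---|---|---|
| 10% | 17.7% vs 13.7% | 4.05 points | 0.77 |
| 20% | 26.9% vs 23.3% | 3.6 points | 0.87 |
| 30% | 36.0% vs 32.9% | 3.15 points | 0.91 |

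The difference is the same as in case A, because s is added to both arms. This is a hybrid illustration: it applies the any-one-sign rule to patients with pneumonia at entry and keeps the planned rates for everyone else.

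**Chance imbalance.** The planned difference is 35 × 0.045 = 1.6 patients. Treating the arms as independent binomial samples, the difference between arms in the number who enter with pneumonia has standard deviation √(2 × 35 × s(1−s)), which is 2.5, 3.3 or 3.8 patients at s = 10%, 20% or 30%. In case B this passes almost one for one into the case count and exceeds the planned effect. In case A, an imbalance of one patient changes expected events by at most 0.086, so it matters little there.

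**The case against.** The strongest reply is that the effect is unquantified and minor. The share with pneumonia at entry is not in the article, which describes the unit only as receiving some polytrauma patients and mostly older people. The planned rates come from an outside study whose denominators are not shown. If those already included patients with pneumonia at entry, multiplying by (1−s) dilutes twice. With 35 per arm, two-sided Fisher power for the planned rates is 2.1% even with nobody in this category, so adding an exclusion would not by itself make phase 2 informative. All of this stands, and it limits the size of the point. It does not remove the mismatch between the entry criteria and the definition of the outcome, which would remain in a correctly sized trial.

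A second reply is that the move of the risk ratio towards 1 in case B belongs to the outcome rule. That also stands in large part. Under a rule that accepts one sign, there is no reason to expect the other patients to stay at 8.6% and 4.1%. Case B should be read as an illustration that overlaps with the outcome-rule problem and should not be counted twice.

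Condensation of a journal article does not explain the gap. The criteria are written out as a list, down to years since stopping smoking, and nothing refers the reader elsewhere for more.

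**Conclusion.** The point holds as an inconsistency between the entry criteria, the Background definition and the phase 2 outcome rule. As written, patients with pneumonia at intubation can be randomised and counted as cases in either arm. With a repaired outcome rule, the cost is in the absolute difference (4.5 points down to 4.05, 3.6 or 3.15) and in power, under the assumed shares and the assumption about what the planned rates represent.

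A reader might infer more than the article supports:

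- *That these patients cannot have a VAP.* A distinct later pneumonia is possible; what the article lacks is a rule to separate it from the one present at entry.
- *That such patients will certainly be enrolled in number.* The article shows only that they are eligible.
- *That the relative effect shrinks towards none whatever the outcome rule.* With a repaired rule the risk ratio stays at 0.48 in expectation.
- *That one arm is favoured.* Randomisation makes the dilution equal between arms in expectation; only chance imbalance remains.

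The point is worth correcting, but it is secondary to the phase 2 sample-size error.

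**What to change.** Either of two changes would do.

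1. Add to the phase 2 exclusion criteria: pneumonia documented at or before intubation, read from the admission record at the eligibility check and before the envelope is opened. Phase 1 criteria need not change, since its main outcome is a bacterial count.
2. Record pneumonia status before randomisation and prespecify the primary phase 2 analysis in patients free of pneumonia at entry. Because status is fixed before allocation, the comparison remains a randomised one.

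With either change, reconcile the Background definition, the eligibility list and the diagnostic rule in Interventions in phase 2, so that all three describe pneumonia that is new since intubation.

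The cost of the first is one eligibility line, a look at the admission record during screening, and somewhat slower phase 2 recruitment. The article says that eligibility is checked but not that this record is read, so that step should be written in. The second keeps recruitment open, but the excluded patients add nothing to the primary analysis and must be allowed for in the sample size. According to Trial status, recruitment has not started and phase 2 is proposed for May 2019, so on that timetable either change can be made before any phase 2 patient is enrolled.
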